| Study Title:                                    | Effects of a sensorimotor training on postural control and pain: A parallel, single-blinded randomised controlled trial.                                                                                                                                                                                                                                                                                                                                                                                                                                                                    |
| Short Title / Study ID:                         | SeMoPoP: Sensorimotor and postural deficiencies in Pain rehabilitation/ 873                                                                                                                                                                                                                                                                                                                                                                                                                                                                                                                 |
| Protocol Version and Date:                      | Version 2.0 dated 31/03/2015                                                                                                                                                                                                                                                                                                                                                                                                                                                                                                                                                                |
| Trial registration:                             | www.kofam.ch (SNCTP000000873)
www.clinicaltrials.gov (NCT02304120)                                                                                                                                                                                                                                                                                                                                                                                                                                         |
| Study category and Rationale                    | Category A: The medical device is CE marked and will be applied according to the specialised information.                                                                                                                                                                                                                                                                                                                                                                                                                                                                                   |
| Clinical Phase:                                 | Observational study and testing of treatment efficacy of a training method.                                                                                                                                                                                                                                                                                                                                                                                                                                                                                                                 |
| Background and Rationale:                       | Sensorimotor training (SMT) is popularly applied as preventive or rehabilitative exercise method in various sports and rehabilitation settings, especially when postural control, linked to proprioception, is suspected to be deficient. Its effect, however, on pain and function is only poorly evaluated.                                                                                                                                                                                                                                                                               |
| Objective(s):                                   | The projects has two main objectives:

 
1. Measure effects of a four- to five- week sensorimotor training intervention, compared to low intensity endurance training, on musculoskeletal pain, functional status, postural control, and proprioception in patients with chronic non-specific low back pain.
 
2. Evaluate the relationship between cervical proprioception, postural control, and chronic non-specific low back pain (CNLBP) compared to healthy controls.
 
                                                        |
| Outcome(s):                                     | Primary outcomes:
Pain & Functional status: Visual Analogue Scale (VAS) and Oswestry Disability Index (ODI)

Secondary outcomes:
Postural Control: Sway of base of support (BOS), centre of pressure of BOS, Centre of Mass, Angular variation of involved segments, Uncontrolled Manifold Index before and after 5-week intervention.

Proprioception: Joint Repositioning Error of cervical, lumbar, hip, knee and ankle joints (before versus after perturbation) and head repositioning sense (HRS) before and after 5-week intervention. |

|                                        |                                                                                                                                                                                                                                                                                                                                                                                                                                                                                                                                                                                                                                                                                                                                                                                                                                                                                                                                                                                                                                                                                                                                                                                                                                                                                                 |
|----------------------------------------|-------------------------------------------------------------------------------------------------------------------------------------------------------------------------------------------------------------------------------------------------------------------------------------------------------------------------------------------------------------------------------------------------------------------------------------------------------------------------------------------------------------------------------------------------------------------------------------------------------------------------------------------------------------------------------------------------------------------------------------------------------------------------------------------------------------------------------------------------------------------------------------------------------------------------------------------------------------------------------------------------------------------------------------------------------------------------------------------------------------------------------------------------------------------------------------------------------------------------------------------------------------------------------------------------|
| Study design:                   | Randomised, single-blinded, parallel controlled trial evaluation and pre- to post intervention comparison with cross-sectional analysis of baseline parameters for comparison to normative values.                                                                                                                                                                                                                                                                                                                                                                                                                                                                                                                                                                                                                                                                                                                                                                                                                                                                                                                                                                                                                                                                                              |
| Inclusion / Exclusion criteria: | 
Inclusion criteria:
 
 
• Patients with clinically confirmed musculoskeletal low back pain (non-specific low back pain)
 
• VAS pain > 0; ODI>0
 
• Age ≥ 18 years
 
 
Exclusion criteria:
 
 
• Known or suspected neurological diseases or lesions
 
• Traumatic injury of musculoskeletal system (fractures, tumours)
 
• Spinal pathologies (e.g., tumour, infection, fracture, and inflammatory disease)
 
• Previous spinal surgery
 
• Presence of any contraindication to exercise (fracture or cardiovascular limitations)
 
• Pain in the neck or cervical spine that reduces active movement to less than 30° rotation to each side
 
• Whiplash during the last year
 
• Known vestibular pathologies
 
 
Healthy group:
 
Participants of the healthy group must be free of neurological or orthopaedic limitations to daily activity (VAS=0; ODI=0).
                                                                                                                                                                                                                      |
| Measurements and procedures:    | 
Interested individuals will be informed (written and personally) and given at least 24 hours of consideration time before being invited to baseline (BL) measurements.
 
Healthy participants will be invited for a single baseline measurement of all primary and secondary outcomes.
 
Patients with CNLBP will be invited to baseline measurements after which they may still decide whether or not they would like to take part in the RCT trial. After a second assessment (pre-intervention, T0), included patients will then be randomly allocated to either the experimental (EG) or the control group (CG). All participating patients will receive standard physiotherapy. CG will receive additional exercise therapy (LIT), the EG will receive additional SMT.
 
One or two days after (T1) and four weeks after (FU) the last treatment, the project leader (PL) or the technical assistant will record the post-intervention assessment of the primary and secondary outcomes.
 
Each assessment will consist of a postural control task (standing on a labile platform and stabilising anticipated anterior-posterior sway), a head-repositioning task, and two questionnaires. Total duration will be approximately one hour.
 |
| Study Product / Intervention:   | 
SMT will be performed with the Posturomed®. The Posturomed is a neuro-orthopaedic therapy device used in rehabilitative and exercise settings to prevent muscular imbalance and promote restitution of functional stability. A 7-stage protocol exists and is instructed by exercise therapists. This particular form of SMT is henceforth termed Postural Proprioceptive Therapy (PPT). Recommendations for home exercise will be provided.
                                                                                                                                                                                                                                                                                                                                                                                                                                                                                                                                                                                                                                                                                                                                                                                                                                             |

|                                               |                                                                                                                                                                                                                                                                                                 |
|-----------------------------------------------|-------------------------------------------------------------------------------------------------------------------------------------------------------------------------------------------------------------------------------------------------------------------------------------------------|
| Control Intervention (if applicable):  | PPT will be compared to a sham intervention (low-intensity endurance training).                                                                                                                                                                                                                 |
| Number of Participants with Rationale: | 20 to 30 patients with low back pain (min. 10 per arm) and 20 healthy controls for the normative data. Based on previous studies with similar endpoints, the selected amount of participants has shown to suffice for an explorative approach with a desired power of 80% and an alpha of 0.05. |
| Study Duration:                        | September 2014 to December 2015                                                                                                                                                                                                                                                                 |
| Study Schedule:                        | Begin recruiting: January 2015
Last assessment: December 2015                                                                                                                                                                                                                                |
| Investigator and project leader:       | [name]
[contact]
[contact]                                                                                                                                                                                   |
| Study Centre:                          | Reha Rheinfelden
[name]

[name]                                                                                                                                                                                                                                   |
| Statistical Considerations:            | Student T-Test will be applied for group comparison at Baseline for cross-sectional comparison of LBP group with healthy group.

Repeated measure ANOVA with post-hoc analysis will be applied to test therapy effects.

Effect size will be calculated with Guyatt's effect size.  |
| GCP Statement:                         | This study will be conducted in compliance with the protocol, the current version of the Declaration of Helsinki, the ICH-GCP or ISO EN 14155 (as far as applicable) as well as all national legal and regulatory requirements.                                                                 |

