### **3.2 Investigational Product (treatment, device) and Indication**

There is a wide variety of ways how SMT can be performed. For this study, proprioceptive postural training (PPT) will be applied using the neuro-orthopaedic therapy device Posturomed®. The Posturomed consists of a labile platform, with adjustable damped swaying behaviour. Media-lateral and antero-posterior sway are increased when the two brakes, one at the front and one at the back, are released. This gives it three specific configurations with increasing levels of instability. The Posturomed® is used for therapy, but has also been used for assessment of postural [22]. In contrast to most proprioceptive training devices, the exercise plan for PPT is clearly defined, quickly explained to the patient and easily understood.

PPT is indicated for postural specific back pain, functional instability of weight-bearing joints (e.g. knee- or ankle instability), hypermobility, and other postural deficiencies. PPT is never applied as a stand-alone therapy but always embedded in multimodal therapy.

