### **3.4 Clinical Evidence to Date**

PPT will be performed using the neuro-orthopaedic therapeutic device Posturomed®. It was marketed in 1993 by a developer of orthopaedic chairs, Haider Bioswing, in collaboration with specialists from physical rehabilitation of pain [9]. It has been used as postural measure balance in a row of intervention studies after its physical characterisation and discriminant validity was confirmed [22, 23]. Combined with a non-contact path measuring system the therapeutic device is deemed to be suitable for characterizing balance abilities in an upright one-legged stance. Low variability of oscillation frequency suggests mechanically caused sway whereas the extent and duration of the oscillation is believed to be caused by the neuromuscular regulation of the subject. Hence, the Posturomed® can be combined with an accelerometer to quantify balance [22, 23].

In an unpublished thesis by Ganz et al. [24], postural control was significantly improved and reduced pain perception and functional impairment were reported. However, co-interventions were not controlled and group allocation was not randomised. Together with the small sample size applied, it is not possible to make any conclusive remarks on the clinical evidence for sensorimotor Training (SMT) effectiveness. Also, after conducting a systematic review on the topic of general SMT in pain rehabilitation [25], it was shown that no high-quality studies exist and that there is inconsistent evidence on the benefits of SMT.

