## 9.2 Assessments of outcomes

### 9.2.1 Assessment of primary outcome

Whilst preparing the setup and software configuration, the subject will be given 10 minutes time to fill in the personal data sheet, including the VAS scales for pain, and the ODI questionnaire for functional status. The questionnaires will be filled in by the patients at every measurement event (BL, T0, T1, and T2).

Self-reported impairment in daily activities will be assessed using the German version of the Oswestry Disability Index (ODI-D), which shows a good reliability. The ODI has ten sections about daily activities (pain, body hygiene, lifting objects, walking, sitting, standing, sleeping, sexual behaviour, social life, and travelling). Each section can be rated from 0 (no pain during activity or pain getting worse) to 5 (I cannot do it myself). The total score is in percentage of the total 50 points, if each section was answered (45, if 9 sections were answered, and so on). The end score will be from 0% (minimal impairment) to 100% (bedridden). A change of 4 points is considered as clinically relevant [26].

Self-reported pain will be assessed using the German version of the Visual Analogue Scale (VAS). It shows a good reliability with a correlation of 0.937 between the first and the second assessment. The VAS is a 100mm line with two endpoints representing the extreme states "no pain" and "pain as bad as it could be". A minimum of 13 mm difference on the scale is considered as clinical relevant [26].

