### 9.2.2 Assessment of secondary outcomes

The secondary outcomes, joint repositioning sense and postural control, will be measured at each measurement event (BL, T0, T1, and T2).

The experimental set-up consists of the neuro-orthopaedic therapy system Posturomed® 202 with handrail (Haider Bioswing, Pullenreuth, Germany), an attached provocation module (Haider Bioswing GmbH, Pullenreuth, Germany), a high-speed camera Basler A602F (Basler AG, Ahrensburg, Germany), a personal computer with Windows 8 operating system to which the camera is attached with USB 3.0, an accelerometer attached to the base-plate of the Posturomed®, and optical markers to measure different joint deflections and joint motion. The markers will be tracked with the motion analysis software Templo (v.7.1.304, Contemplas GmbH, Kempten, Germany). COP is measured by means of a Zebris FDM-S force measuring plate on top of the swaying platform.

After evaluating primary outcomes, the participants will be equipped with markers as shown in Figure 2 below. After familiarisation with the Posturomed's labile surface, he or she will be instructed to adopt an upright posture with the arms folded across the chest (in order to keep hip markers visible). On the cue "ready-steady-go", the assessor will release the platform from its 5 cm deflection. The swaying is recorded until complete damping of the oscillation has occurred (approximately 15

seconds). As participants will be standing on both feet, any facilitation of the task through engaging brakes would make the task too easy (as tested in pre-pilot tests). Hence, all of the device's brakes will be released for this test allowing maximal sway. The camera setup will record the entire task. The task will be repeated five times for each patient. The arithmetic mean of the five trials will be used for further analysis.

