### 9.2.3 Assessment of other outcomes of interest

At BL socio-demographic data will be recorded to characterise the included patients (age, gender, activity level, and profession).

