## **11.4 Planned Analyses**

Baseline imbalance between groups will be tested with a student t-test. Differences in means between healthy participants and patients with CNLBP will be analysed with independent student t-tests. A mixed (2) Group x (2) ME ANOVA with repeated measures during ME will be conducted for each dependent variable individually (Pain VAS, Functional Status ODI, Postural Control COM and CM, Proprioception JRE, and Motor Equivalence UCM).

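### Body mass and height are not among the listed baseline data, so a body-size difference could mimic or mask a difference in platform sway and COP between patients and healthy controls

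*Protocol*

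**What the plan says.** **Device and test.** Protocol section 3.2: "The Posturomed consists of a labile platform, with adjustable damped swaying behaviour". In section 9.2.2 every participant stands on both feet, all brakes are off, and the platform is released from the same 5 cm deflection. "The swaying is recorded until complete damping of the oscillation has occurred", which takes roughly 15 seconds. In the same section, "COP is measured by means of a Zebris FDM-S force measuring plate on top of the swaying platform".

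**Outcomes.** Section 5.2 names COP, platform sway and the UCM index as secondary endpoints. The synopsis adds COM: "Sway of base of support (BOS), centre of pressure of BOS, Centre of Mass". The synopsis also says that healthy participants have one baseline measurement of all primary and secondary outcomes, so these measures feed the comparison with patients as well as the trial.

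**Data collected.** Section 9.2.3: "At BL socio-demographic data will be recorded to characterise the included patients (age, gender, activity level, and profession". Body mass, height and BMI do not appear anywhere in the text. Section 9.2.1 mentions a sheet on which participants "fill in the personal data sheet, including the VAS scales for pain", and its other contents are not given.

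**Comparison.** Section 7.2 recruits healthy people by advertisement and staff notice board, without matching. Section 11.4: "Differences in means between healthy participants and patients with CNLBP will be analysed with independent student t-tests". No covariate or scaling is mentioned.

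**The concern.** Research question 2 in section 4 asks whether patients have poorer postural control than healthy people. The measuring instrument is a mechanical oscillator with the participant as part of its load. If patients and volunteers differ in body mass, sway and COP can differ between the groups even when neuromuscular control is the same. If the mass difference runs the other way, a real difference can be hidden.

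Section 3.4 shows how such a result would be read. It treats oscillation frequency as mechanical, but says "the extent and duration of the oscillation is believed to be caused by the neuromuscular regulation of the subject". In a damped system duration also has a mechanical part that rises with mass.

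This cannot simply be left to a later analysis plan, because a covariate can be used only if it was collected. Each healthy participant is seen once, so an omission at that visit may be hard to repair. The patient-versus-healthy comparison is one of the two main objectives in the synopsis.

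**Working it through.** **1. The protocol's own figure.** The only power figure tied to the postural-control hypothesis is in section 11.2: above 0.9, from N = 9, a mean difference of 0.055 and an SD of 0.015.
- Paired effect = 0.055/0.015 = 3.67, noncentrality 3.67 × √9 = 11, power above 0.999.
- From the quoted F of 25.8: √(25.8/9) = 1.69, power 0.993.

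The figure is reproduced. However, it is a within-subject contrast in healthy people and says nothing about the spread of sway or COP between patients and controls.

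**2. Why mass enters.** Assume a linear, viscously damped platform. Amplitude then decays with time constant 2M/c, where M is the total moving mass and c the damping. The documents give neither. For an assumed 80 kg person against a 70 kg person, both fully coupled to the platform:

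| Assumed platform mass | Ratio of decay times |
|---|---|
| 0 kg | 80/70 = 1.143 |
| 15 kg | 95/85 = 1.118 |
| 30 kg | 110/100 = 1.100 |

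Decay is 10% to 14% longer with no difference in control. If the platform is spring-restored, frequency falls by 4.7% (√(100/110) = 0.953) to 6.5% (√(70/80) = 0.935). For a pure pendulum suspension, frequency would not change with mass. This shows the mechanism; decay time itself is not a defined outcome.

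**3. Effect on the t-test.** Let D be the body-size difference between groups in SD units, and r the within-group correlation of body size with the outcome. With no true difference in control, the standardised bias is r × D. The noncentrality is r × D × √(n₁n₂/(n₁+n₂)), on n₁+n₂−2 degrees of freedom, two-sided 5%. D and r are assumptions. Group sizes are from the protocol: the synopsis gives 20 healthy and 20 to 30 patients, while section 11.2 gives 10 healthy and 20 patients.

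Middle case, D = 0.5 and r = 0.5, bias 0.25 SD:

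| Patients, healthy | Noncentrality | Rejection of a true null | Difference detectable with 80% power |
|---|---|---|---|
| 20, 10 | 0.25 × 2.582 = 0.65 | 9.6% | 1.12 SD |
| 20, 20 | 0.25 × 3.162 = 0.79 | 12.0% | 0.91 SD |
| 30, 20 | 0.25 × 3.464 = 0.87 | 13.6% | 0.83 SD |

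Over D = 0.3 to 0.8 and r = 0.3 to 0.7, rejection runs from 5.6% to 28.7% (20, 10), 5.9% to 40.8% (20, 20) and 6.1% to 47.7% (30, 20).

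The middle-case bias is 22% to 30% of the detectable difference (0.25/1.12 to 0.25/0.83). That is material, but it does not by itself make a false finding likely.

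**The case against.** Several points limit the concern, and most of them stand.

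- **Hypothesis 2.** A reader might infer that body size undermines hypothesis 2 directly. Section 11.1 words that hypothesis as joint-configuration variability when adjusting COM, and as a two-sided difference. That is the joint-angle (UCM) construct, which mass affects only indirectly. Research question 2 is the better target.
- **Which variables are tested.** The list of dependent variables in section 11.4 belongs to the ANOVA and names neither sway nor COP. The t-test sentence names no variables. Sway and COP are nevertheless secondary endpoints measured in healthy participants.
- **Section 3.4.** The remark on extent and duration is background from device work in one-legged stance; this trial tests on both feet. The section also reports that the device's physical characterisation and discriminant validity were confirmed. Whether that work covered load dependence cannot be judged here.
- **Whether body size is available.** A reader might infer that it is never recorded and cannot be recovered. The documents support only that it is not listed. The personal data sheet is unspecified, and the force plate and markers might yield mass and segment lengths, although no such use is planned.
- **A larger figure.** Carrying the decay-time model through to a test result is tempting. Take patients 5 to 10 kg heavier than 70 kg, a 15 to 30 kg platform, 50% to 100% of body mass coupled, and a CV of 15% to 30%. Decay is then 3.8% to 11.8% longer, or 0.13 to 0.78 SD, and rejection is 7% to 68% at 20 against 20. Every input is assumed. At the top end a body-mass SD of 0.15 × 85 = 12.75 kg would use up the whole CV, leaving no variation for neuromuscular control.
- **Height.** The argument that COM excursion scales with height is plausible, but no size can be put on it.
- **Over-adjustment.** If body mass is related to both back pain and control, adjusting may remove real signal.

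None of this removes the core: unmatched groups, an unadjusted test, a measure with a mass-dependent component, and no body size on the list.

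**Conclusion.** The point holds in a limited form. For sway and COP, and less directly for COM, the patient-versus-healthy comparison is open to confounding by body size, and the listed data provide no means of examining it. UCM is affected only indirectly. A reader might extend the concern to the treatment effect. That is not supported, because allocation is random and the ANOVA uses each patient's own change, so the randomised comparison is largely unaffected.

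The size cannot be derived from the documents. Under an assumed moderate imbalance and correlation (0.5 SD and 0.5), a nominal 5% test would reject a true null in about 10% to 14% of studies. With small D and r the excess is negligible. The dependence on mass rests on a linear damped model that the protocol does not state. This is an inexpensive improvement to an exploratory comparison, not a flaw that invalidates the study.

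**What to change.** - **Section 9.2.3:** list body mass and height at BL, and word the sentence to cover healthy participants as well as patients. If the personal data sheet already holds them, say so here.
- **Section 11.4:** add that sway, COP and COM will be compared between healthy participants and patients with adjustment for body mass, and for height either as a covariate or by scaling, with the unadjusted t-test shown beside it.

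The cost is two numbers per participant at a visit that already takes place, one sentence of analysis, and up to two degrees of freedom in a small sample. Showing both results guards against over-adjustment, since the reader can see how far the conclusion depends on body size. Nothing changes in treatment or in the randomised analysis.
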